### Additional consent provisions for collection and use of participant data and biological specimens {26b}

A total of 300 pregnant women will be included in a sub-study of the immune response to the vaccine. From the mother, we will collect samples of blood, cord blood, and breast milk. We will also seek permission to collect a small sample of blood from 75 babies [born to mothers that receive study vaccine during pregnancy] when they are 3 months old. We will ask permission to keep any remaining samples for future studies.

## Interventions

### Explanation for the choice of comparators {6b}

The comparator group is unvaccinated pregnant women (group B). Robust data on background rates of adverse pregnancy outcomes are not available. Therefore, the unvaccinated pregnant women in group B (a non-interventional control) are important to establish the frequency and magnitude of changes in clinical endpoints that may occur in the absence of active vaccination during pregnancy (group A). Group B comparator women will receive the study vaccine after pregnancy termination.

### Intervention description {11a}

The Ebola vaccine regimen in this trial is comprised of two vaccines:Ad26.ZEBOV is a replication-incompetent monovalent vaccine encoding the full-length glycoprotein (GP) from Ebola virus (EBOV) Mayinga. A 0.5-mL injection into the deltoid muscle in the upper arm (or thigh if needed) of 5 × 10^10^ vp will be administered at day 1 (enrollment).MVA-mBN226B, further referred to as Modified Vaccinia Ankara (MVA)-BN®-Filo, does not replicate in human cells and is a multivalent vaccine encoding the EBOV GP, the Sudan virus (SUDV) GP, the Marburg virus (MARV) Musoke GP, and the Taï Forest virus (TAFV, formerly known as Côte d’Ivoire ebolavirus) nucleoprotein (NP). A 0.5 mL injection into the deltoid muscle in the upper arm (or thigh if needed) of 1 × 10^8^ InfU will be administered at day 57 (− 14 days + 28 days) after the Ad26.ZEBOV dose.

The second dose of vaccine should ideally be given in the opposite arm/thigh (unless the opposite arm/thigh has a condition that prevents evaluation of the arm/thigh after injection). The Ad26.ZEBOV and MVA-BN-Filo vaccines will be manufactured and provided under the responsibility of Janssen Vaccines and Prevention B.V.

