^p^In case pregnancy completion/termination in a group A pregnant woman occurs prior to receipt of dose 2, visits 9 and 10 should be performed: visit 10 being relative to visit 9 (2 day window). Visit 5 (dose 2 vaccination with a window of – 14 days, + 28 days) should in this case be performed after visit 9, with visits 6 and 8 being relative to actual dose 2 receipt (visit 5). All of these visits should be captured in RedCap cloud in addition to source documentation. Reactogenicity data (diary completion) should still be performed following dose 2 for group A women that have a pregnancy completion/termination prior to receipt of dose 2

**Table 3 Tab3:** Schedule of activities—women in group B

Visit #	1	2	3	4	5	6	7	8	9^a^	10^n^	11 ^a^	EE
**Visit timing**^**p**^		**Randomiz-ation (D1)**	**D1 + 28 days**	**D1 + 56 days**	**D1 + 12 weeks**	**Pregnancy completion/** **termination**	**Dose 1**	**Dose 2**	**Dose 2 + ** **21 days**	**Dose 2 + ** **28 days**	**Dose 1 + ** **365 days**	**Early** **exit**
**Visit day and window**	**-28 to 1**	**D1**	**D29 ± 7 days**	**D57** ** − 14 days, + 28 days**	**D85 ± 7 days**	**PP 1** ^b^ ** + 2 days**	**PP 43** ^c^ ** + 28 days**	**PP 99** **-14 days, + 28 days**	**PP 120** ** ± 14 days**	**PP 127** ** ± 3 days**	**Dose 1 + 365 ± 28 days**	
**Visit type**	Screening	**Random-ization**	Safety	Safety	Safety	Safety and immuno	**DOSE 1 group B**	**DOSE 2 group B**	Safety and immuno	Safety	Safety and immuno	Early exit
Assessment of understanding	•											
Written informed consent (ICF) ^d^	•											
Inclusion/exclusion criteria	•	•										
Demographics ^**e**^	•											
Medical and obstetric history ^f^ and prestudy meds	•											
Physical examination ^f^	•						•	•				•
Obstetric exam ^f^	•	•				•						•^o^
Targeted physical examination ^f^		•	•	•	•				•	•	•	
Vital signs ^f^ incl. body temperature	•	•	•	•	•	•			•	•	•	•
Urine pregnancy test ^g^	•											
Hematology, chemistry ^g^	•											
Urine dipstick/urinalysis ^g^	•	•	•	•	•							
Syphilis, HIV, hepatitis B and C, malaria screening ^g^	•											
Obstetric ultrasound ^h^	•	•^h^			•							•^o^
Biometric scan		•	•	•	•	•	•	•	•	•	•	•
Contact information	•	•	•	•	•	•	•	•	•	•	•	•
Randomization		•										
Pre-vaccination symptoms^i^												
Vaccination							•	•				
30 min post-vaccination observation ^j^							•	•				
Adverse maternal, fetal outcomes		•	•	•	•	•	•					
SAE recording		•	•	•	•	•	•	•	•	•	•	•

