Concomitant medications ^k^	•	•	•	•	•	•	•	•	•	•	•	•
Delivery history ^l^						•						
Post pregnancy physical examination ^l^						•						
Laboratory assessments ^m^						•						
Group B immunology subset supplemental procedures (*N* = 150)	**1**	**2**	**3**	**4**	**5**	**6**	**7**	**8**	**9**	**10**	**11**	EE
Humoral immunogenicity sample (serum)									•		•	
Breast milk sample (*N* = 10)												

pre-dose;

pre- and post-dose

^a^Visits 9 and 11 for group B immunology subset participants only

^b^PP1 refers to the day of pregnancy completion/termination. Visit 6 (PP1) should occur on the day of pregnancy completion/termination or within 2 days

^c^Visit 7 (PP 43) scheduled to occur at routine 6 week post-partum visit

^d^Must be signed before first study-related activity

^e^Maternal demographic information to be collected at screening includes: date of birth, race/ethnicity, education level, geographical location/residence, occupation, household size (number of persons living in the same home), and international travel history

^f^Information to be collected for medical and obstetric history, physical exams, and vital signs is specified in the protocol

^g^Urine dipstick for protein and glucose results will be performed at these visits. If results are 1 + or greater, then additional work-up for pre-eclampsia or gestational diabetes may be warranted

^h^Ultrasound not required at visit 2 if screening (visit 1) ultrasound completed within past 10 days and no other indication for ultrasound

^i^Investigator must check for acute illness or body temperature ≥ 38.0 °C at the time of vaccination. In such cases, the participant may be vaccinated at later time point

^j^Participants will be closely observed for a minimum of 30 min post-vaccination

^k^Includes any medical treatment/medications given to the mother during delivery (e.g., antibiotic prophylaxis)-specifying names of medications administered

^l^Information to be collected for delivery history and post-pregnancy examination is specified in the protocol

^m^Any routine laboratory assessment performed at time of delivery and other laboratory tests as medically indicated

^n^Visit 10: for women not part of the immunogenicity subset this visit will be the end of the trial

^o^Not required if participant is not pregnant

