^p^If pregnancy completion/termination in a group B woman occurs prior to performing all in-pregnancy protocol visits, these missed visits will not be considered as protocol deviations

**Table 4 Tab4:** Schedule of activities—women From Umurinzi

Visit #	1	2	3	4	5	EE
**Visit timing**		**Dose 2**	**Dose 2 + 28 days**	**Pregnancy completion/termination**	**PP 1 + 42 days**	**Early** **exit**
**Visit day and window**	** − 28 to 1**	**D57** ** − 14 days, + 28 days**	**D85 ± 7 days**	**PP 1** ^a^ ** + 2 days**	**PP 43** ^b^ ** ± 14 days**	
**Visit type**	Screening	**Dose 2**	Safety	Safety and immuno	Safety	Early exit
Assessment of understanding	•					
Written informed consent (ICF) ^c^	•					
Inclusion/exclusion criteria	•					
Demographics ^d^	•					
Medical and obstetric history ^e^; pre-pregnancy and pre-study meds	•					
Physical examination ^e^	•				•	•
Obstetric exam ^e^	•	•		•		•^m^
Targeted physical exam ^e^		•	•			
Vital signs ^e^ incl. body temperature	•		•	•	•	•
Urine pregnancy test ^f^	•					
Hematology, chemistry ^f^	•					
Urine dipstick/urinalysis ^f^	•	•	•			
Syphilis, HIV, hepatitis B and C, malaria screening ^f^	•					
Obstetric ultrasound ^g^	•		•			•^m^
Biometric scan	•	•	•	•	•	•
Contact information	•	•	•	•	•	•
Pre-vaccination symptoms ^h^						
Vaccination		•				
30 min post-vaccination observation^i^		•				
Adverse maternal, fetal outcomes		•	•	•	•	
SAE recording		•	•	•	•	•
Concomitant medications ^j^	•	•	•	•	•	•
Delivery history ^k^				•		
Post pregnancy physical examination ^k^				•		
Laboratory assessments ^l^				•		

pre-dose;

pre- and post-dose

^a^PP 1 refers to the day of pregnancy completion/termination. Visit 4 (PP 1) should occur on the day of pregnancy completion/termination or within 2 days

^b^Visit 5 (PP 43) scheduled to occur at routine 6 week post-partum visit

^c^Must be signed before first study-related activity

^d^Maternal demographic information to be collected at screening includes: date of birth, race/ethnicity, education level, geographical location/residence, occupation, household size (number of persons living in the same home), and international travel history

^e^Information to be collected for medical and obstetric history, physical exams, and vital signs is specified in the protocol

^f^Urine dipstick for protein and glucose will be performed at these visits. If results are 1 + or greater, additional work-up for pre-eclampsia and gestational diabetes may be warranted

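### Table 3 times both group B doses from delivery, so its windows alone allow 14–84 days between doses where the regimen description and Table 2 give 42–84, and the article does not say which governs

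*Protocol article*

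**What the plan says.** Intervention description {11a} describes the regimen for the whole trial. The first vaccine "vp will be administered at day 1 (enrollment"), and the second, at 1 × 10^8 "InfU will be administered at day 57", has a window of −14/+28 days counted from the Ad26.ZEBOV dose. Table 2 repeats this for group A: dose 1 on D1, dose 2 on D57, −14/+28 days.

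Table 3 schedules group B differently. PP 1 is the day the pregnancy ends. Dose 1 is visit 7, at PP 43 + 28 days; footnote c reads "Visit 7 (PP 43) scheduled to occur at routine 6 week post-partum visit". Dose 2 is visit 8, at "PP 99 -14 days, + 28 days". The visit 8 column is headed only Dose 2. Visits 9, 10 and 11 are headed Dose 2 + 21 days, Dose 2 + 28 days and Dose 1 + 365 days, but visits 9 and 10 also carry fixed postpartum days: PP 120 ± 14 and PP 127 ± 3.

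For group A women who deliver before dose 2, footnote p of Table 2 re-times later visits, "with visits 6 and 8 being relative to actual dose 2 receipt (visit 5"). Footnote p of Table 3 covers only in-pregnancy visits missed because the pregnancy ended early: "these missed visits will not be considered as protocol deviations". No Table 3 footnote ties group B's dose 2 to the day dose 1 was given.

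**The concern.** The −14/+28 day tolerance suits a schedule anchored on dose 1. Table 3 applies it to a schedule anchored on delivery, where dose 1 already has a 28-day tolerance of its own. The two tolerances add up, so the minimum interval shrinks by one day for each day that dose 1 is late.

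Group B women, vaccinated after delivery, are the non-pregnant comparator for the secondary immunogenicity objective, with 150 women per arm and 21 days after dose 2 as a named sampling time. A site working from Table 3 alone could give an interval under 42 days in that arm only, which would mix dose interval with pregnancy status. The same site could record as out of window a dose 2 that complies with the regimen description. The per-protocol immunogenicity (PPI) set excludes major deviations expected to affect immunogenicity, so it matters which interval rule defines a deviation. The background section also rests the inferred protective effect on data from the 8-week interval.

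**Working it through.** **Inputs.** Regimen description and Table 2: dose 1 on day 1, dose 2 on day 57, −14/+28. Table 3: dose 1 on PP 43 + 28 days, dose 2 on PP 99, −14/+28; visit 9 on PP 120 ± 14; visit 10 on PP 127 ± 3.

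**The stated interval.** Earliest 57 − 14 − 1 = 42 days; target 57 − 1 = 56 days (8 weeks); latest 57 + 28 − 1 = 84 days. Reading day 57 as 57 elapsed days gives 43 to 85, which does not change the point.

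**Table 3 windows.** Dose 1: PP 43 to 43 + 28 = 71. Dose 2: PP 99 − 14 = 85 to 99 + 28 = 127, which is 43 days. Shortest interval 85 − 71 = 14 days; nominal 99 − 43 = 56; longest 127 − 43 = 84.

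**Mismatch by day of dose 1.** For dose 1 on PP d, the regimen rule allows dose 2 on PP d + 42 to d + 84, and Table 3 allows PP 85 to 127. The overlap runs from d + 42 to 127, which is 86 − d days. On each side d − 43 days disagree: Table 3 allows that many days that the regimen rule forbids, and excludes as many that it allows.

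| Dose 1 | Table 3 interval (days) | Regimen rule, dose 2 | Overlap (days) | Mismatch each way (days) |
|---|---|---|---|---|
| PP 43 | 42–84 | PP 85–127 | 43 | 0 |
| PP 57 | 28–70 | PP 99–141 | 29 | 14 |
| PP 71 | 14–56 | PP 113–155 | 15 | 28 |

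An exact 8-week dose 2 falls on d + 56 = PP 99 to 127, so it always satisfies both rules.

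**Later visits.** Visit 9's window is PP 106–134 and visit 10's is PP 124–130. With an exact 8-week dose 2:

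- Dose 2 + 21 days is d + 77. This exceeds 134 when d ≥ 58, i.e. 14 of the 29 permitted dose 1 days.
- Dose 2 + 28 days is d + 84. This exceeds 130 when d ≥ 47, i.e. 25 of the 29.

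Table 3 also disagrees with its own headings. A dose 2 on PP 127 is permitted, yet dose 2 + 21 days is then PP 148, against a visit 9 window that ends on PP 134.

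**The case against.** The strongest reply is that the regimen description is general. Its dose 2 clause counts from the first vaccine, Table 4 repeats the same day 57 window for the women from Umurinzi, and Table 3's nominal days are exactly 56 apart with the same tolerance. On that reading Table 3 shows an on-time schedule, the interval rule applies as well, and a woman must satisfy both. The two windows always overlap, so a careful site can comply. Dose 1 is meant for the routine 6-week visit, where the mismatch is zero, and 14 days needs the last permitted dose 1 day combined with the first permitted dose 2 day. A tighter calendar limit on late doses is also something a sponsor may choose. Finally, this is a condensed article, and the full protocol may settle the matter.

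Much of this limits the size of the problem, but it does not remove it. That both rules apply together is a possible reading which the article does not state. Placing dose 1 at enrollment cannot describe group B, who are vaccinated only after pregnancy, so a reader may reasonably take Table 3 as that arm's schedule. If the postpartum days are only nominal, the windows printed beside them, such as ± 3 days at visit 10, have no clear meaning. Nor is this merely a detail left to the full protocol: both rules are printed in the article, and they give different answers.

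**Conclusion.** The concern holds. Table 3's windows alone permit 14 to 84 days between group B doses, against 42 to 84 in the regimen description and in Table 2, and the article states no precedence. The mismatch grows from 0 days each way for dose 1 on PP 43 to 28 days each way on PP 71.

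The calculation takes the printed windows as binding. The article gives no distribution of dose 1 days, so the number of women affected is unknown. It also gives no figure for how the interval changes antibody concentration, so the size of any bias cannot be stated. The comparison at risk is secondary and descriptive, with no formal test. The primary maternal/fetal outcomes are not affected, because Table 3 collects them in group B only through visit 7, when dose 1 is given. This should be fixed, but it does not threaten the trial's main result.

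**What to change.** In Table 3, set group B dose 2 at the actual dose 1 + 56 days, −14/+28, which gives 42 to 84 days in both arms. Time visits 9 and 10 from the actual dose 2, as their headings already imply. Use this single interval rule in both arms when judging deviations for the PPI set.

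In the article this is a correction or one footnote. If the full protocol carries the same table, the change needs a formal amendment with ethics approval. The latest permitted dose 2 moves from PP 127 to 71 + 84 = PP 155, and visit 10 for such a woman to about 155 + 28 = PP 183. An exact 8-week dose still falls on or before PP 127.

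Recruitment was expected to finish in January 2022, before the article appeared, so some group B doses may already have been given. For those women the single rule can still be applied when the PPI set is defined, and the actual dose interval can be tabulated by arm.

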### Criteria for discontinuing or modifying allocated interventions {11b}

Participants will be withdrawn from study vaccine administration for the reasons listed below. These participants must not receive any additional dose of study vaccine but should enter the follow-up phase with assessments of safety and immunogenicity. Dose modification is not applicable in this study.Any related AEs, worsening of health status or intercurrent illnesses that, in the opinion of the investigator, required discontinuation from study vaccineConfirmed EVDAnaphylactic reaction following vaccinationInjection site ulceration, abscess, or necrosis considered to be related to study vaccineGeneralized urticaria within 72 h of vaccination considered to be related to study vaccineSAEs or other potentially life-threatening (grade 4) event that is determined to be related to study vaccineChronic or recurrent use of immunosuppressants (after discussion with the sponsor)

### Strategies to improve adherence to interventions {11c}

To reduce the chances of a participant being lost to follow-up, prior to randomization attempts should be made to obtain contact information from each participant. The following actions must be taken if a participant fails to return to the study site for a required study visit:The study-site personnel must attempt to contact the participant to reschedule the missed visit as soon as possible, to counsel the participant on the importance of maintaining the assigned visit schedule, to ascertain whether the participant wishes to or should continue in the studyBefore a participant is deemed lost to follow-up, the investigator or designee must make every reasonable effort to regain contact with the participant (where possible, 3 telephone calls, e-mails, and/or SMS/text, or local equivalent methods). These contact attempts should be documented in the participant’s medical recordsShould the participant continue to be unreachable, they will be considered to have withdrawn from the study

Women will receive 12,000 Rwanda Francs for each study visit, equal to roughly $12 USD.

### Relevant concomitant care permitted or prohibited during the trial {11d}

Use of any experimental medication (including experimental vaccines other than the study vaccine) during the study is not allowed. Vaccination with licensed live attenuated vaccines within 4 weeks of a study vaccination (i.e., before or after) is prohibited. Non-live, licensed vaccines (e.g., tetanus, hepatitis A, hepatitis B, rabies) should be given at least 7 days before or 7 days after administration of study vaccine in order to avoid potential confusion of adverse reactions and potential immune interference. If a vaccine is indicated in a post-exposure setting (e.g., rabies or tetanus), it must take priority over the study vaccine. Chronic (> 10 days) or recurrent use of immunomodulators/suppressors, e.g., cancer chemotherapeutic agents, systemic corticosteroids is prohibited during the study and 6 months before the planned administration of the first dose of study vaccine. Ocular, topical, or inhaled steroids are allowed.

### Provisions for post-trial care {30}

Since this trial is enrolling healthy pregnant female participants for which the study vaccine is envisaged to be prophylactic, post-trial care will entail medical follow-up of any continuing SAEs until resolution or stabilization. In the event of trial-related harm or injury, medical care and follow-up will be arranged for affected trial participants at no cost to them. Clinical trial insurance has also been procured for this trial in accordance with national regulations in the participating country (Rwanda).

### Outcomes {12}

As described in Table 1, primary outcomes will be adverse maternal, fetal, and neonatal/infant outcomes in all pregnant women and their neonates/infants. Secondary outcomes will be the description of all serious AEs occurring in all pregnant women and their neonates and the description of all solicited (reactogenicity) and unsolicited AEs (up to 28 days following each vaccination) in all pregnant women from group A. The Brighton Collaboration case definitions for specific adverse maternal/fetal and neonatal outcomes will be used as recommended to provide robust safety evaluation which can be utilized across studies and populations. In a subset of 300 women from group A (*N* = 150) and group B (*N* = 150), immunogenicity will be assessed as secondary outcome. Additionally, persistence of maternal antibodies will be assessed as a secondary outcome in a convenience sample of 75 infants born to group A women in the immunogenicity subset. As an exploratory outcome, if an assay becomes available the presence of antibodies will be assessed in breastmilk in a convenience sample of 50 women from the group A immunogenicity subset who are able to express breastmilk at the time point indicated in the schedule of activities and 10 control women (women in group B before vaccination). Analysis metrics, method of aggregation, and time point for analysis of each outcome are described in the “Statistical methods” section.

**Table 1 Tab1:** Trial objectives and endpoints

Objectives	Endpoints
**Primary**	
• Assess **adverse maternal/fetal outcomes in pregnant women** randomized to receive the 2-dose Ebola vaccine regimen (Ad26.ZEBOV, MVA-BN-Filo (group A)) and in control women (unvaccinated pregnant women (group B))	• Frequency of maternal death, spontaneous abortion, stillbirth, pathways to preterm birth (premature preterm rupture of membranes, preterm labor, insufficient cervix, provider initiated preterm birth), pre-eclampsia/eclampsia, antenatal bleeding and post-partum hemorrhage from randomization until 6 weeks post-completion/termination of pregnancy
• Assess **adverse neonatal/infant outcomes in neonates/infants** born to women randomized to receive the 2-dose Ebola vaccine regimen (Ad26.ZEBOV, MVA-BN-Filo (group A)) and in neonates/infants born to control women (unvaccinated pregnant women (group B))	• Frequency of major congenital malformations, small for gestational age (SGA), low birth weight, preterm birth, neonatal death, and failure to thrive in infants measured from birth until 14 weeks of age

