**Secondary**	
• Assess safety **in pregnant women** randomized to receive the 2-dose Ebola vaccine regimen (Ad26.ZEBOV, MVA-BN-Filo group A) and in control women (unvaccinated pregnant women (group B))	• Frequency and relatedness of all SAEs in women from randomization until study end
• Assess safety **in neonates/infants born** to women randomized to receive the 2-dose Ebola vaccine regimen (Ad26.ZEBOV, MVA-BN-Filo (group A)) and in neonates/infants born to control women (unvaccinated pregnant women (group B))	• Frequency and relatedness of all SAEs in the newborns from birth until study end
• Assess the **reactogenicity** and unsolicited AEs of the 2-dose Ebola vaccine regimen (Ad26.ZEBOV, MVA-BN-Filo) in all vaccinated pregnant women (group A)	• Reactogenicity, defined as local and systemic solicited AEs occurring within 7 days after each dose, and unsolicited AEs within 28 days after each dose: ○ Frequency, grade, duration and causality for solicited systemic AEs and unsolicited AEs ○ Frequency, grade and duration for solicited local AEs
• Describe all pregnancy outcomes	• Pregnancy outcomes (example: normal delivery, Caesarian Section)
• Assess the **immunogenicity** of the 2-dose Ebola vaccine regimen (Ad26.ZEBOV, MVA-BN-Filo) in 150 pregnant women who are anticipated to receive both vaccine doses within the course of their pregnancy (a subset of the 1000 pregnant vaccinated women from group A) compared to 150 non-pregnant women vaccinated after delivery (a subset of group B)	• Anti-EBOV GP binding antibody concentrations, in ELISA units/mL (FANG ELISA) from: ○ Blood samples taken at pre-dose 1, 21 days post-dose 2, at delivery (group A subset only), and 1 year post-dose 1 ○ Cord blood if feasible from women in the group A subset
• Assess **persistence of maternal antibodies** in 75 infants born to women from the group A subset	• Anti-EBOV GP binding antibody concentrations, in ELISA units/mL (FANG ELISA) from a blood sample taken at 14 weeks of age

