^g^Ultrasound not required at visit 2 if screening (visit 1) ultrasound completed within past 10 days and no other indication for ultrasound

^h^Investigator must check for acute illness or body temperature ≥ 38.0 °C at the time of vaccination. In such cases, the participant may be vaccinated at later time point

^i^Participants will be closely observed for a minimum of 30 min post-vaccination

^j^Includes any medical treatment/medications given to the mother during delivery (e.g., antibiotic prophylaxis)-specifying names of medications administered

^k^Information to be collected for delivery history and post-pregnancy examination is specified in the protocol

^l^Any routine laboratory assessment performed at time of delivery and other laboratory tests as medically indicated

^m^Not required if participant is not pregnant

**Table 5 Tab5:** Schedule of activities—neonates/infants from groups A, B, and Umurinzi

Visit #	1 ^a^	2 ^b^	3
**Visit timing**	**Pregnancy completion/termination**	**PP1 + 42 days**	**PP1 + 98 days**
**Visit day and window**	**PP 1** ** + 2 days**	**PP 43** ** ± 14 days**	**PP 99 ± 14 days**
**Visit type**	Safety	Safety	Safety and immuno
Fetal monitoring during labor^c^	•		
Birth outcome^d^	•		
Apgar score^e^	•		
Neonatal physical exam^f^	•		
Medication^g^	•	•	•
Nutrition^h^	•	•	•
Infant physical exam ^f^		•	•
Adverse neonatal/infant outcomes	•	•	•
SAE collection	•	•	•
Humoral immunogenicity sample (serum)^i^			•

^a^Visit 1 (PP 1) should occur on the day of pregnancy completion or within 2 days

^b^Informed consent for any study procedures to be performed for infants ≥ 28 days of age will be obtained from mother at enrolment

^c^Record key findings of fetal monitoring such as fetal position at delivery, gestational age, complications, fetal heart rate, and uterine contractions during labor

^d^Live birth, stillbirth, neonatal death, parity

^e^Measured at 1, 5, and 10 min

^f^Information to be collected for neonatal physical examination and infant physical examination is specified in the protocol

^g^Any medical or intervention given to the neonate (e.g., antibiotic treatment, exchange transfusion, intravenous fluids, steroids or other immunosuppressive therapies, herbal remedies, respiratory support)

^h^Type of feeds (e.g., breast milk (mother/donor), formula feeding, parenteral nutrition, mixed feeding) and their respective start and stop times should be recorded in months of age

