## Statistical methods

### Statistical methods for primary and secondary outcomes {20a}

For purposes of analysis, the following populations are defined:Full analysis set (FAS): The FAS will include all randomized participants. All safety analyses will be made on the FASPer-protocol immunogenicity (PPI): The PPI population will include all randomized and vaccinated participants for whom immunogenicity data are available excluding participants with major protocol deviations expecting to impact the immunogenicity outcomes

Of note, women enrolled from Umurinzi will be analyzed separately. No formal statistical testing is planned. The number and percentage of participants screened, enrolled, randomized, receiving two vaccine doses, and completing follow-up will be summarized by study arm.

Baseline demographic characteristics (including gestational age and obstetric risk assessment) will be tabulated overall and by study arm.

The frequency and percentage of women for whom at least one of the indicated adverse outcomes was reported as a primary endpoint (see above) will be summarized by study group. For each separate adverse maternal/fetal and adverse neonatal/infant outcome, the number and percentage of participants who experience at least 1 occurrence of the given event will also be tabulated by study group (groups A and B, and their infants). The verbatim terms used in the CRF by investigators to identify AEs will be coded using the Medical Dictionary for Regulatory Activities (MedDRA). The reporting of the categorical safety data will include the incidence, severity, relatedness, and type of AEs. Continuous safety parameters will be analyzed descriptively (showing the mean, standard deviation, median, and quartiles [Q1 and Q3]).

For participants from group A, all reported AEs, events-related diary information (solicited local at injection site and systemic, and unsolicited) with onset within 4 weeks post dose 1 or dose 2 vaccination (i.e., treatment-emergent AEs) will be included in the analysis. For each AE, the number and percentage of participants who experience at least 1 occurrence of the given event will be summarized. Of note, solicited and unsolicited AEs will not be collected for group B participants.

Summaries, listings, datasets, or participant narratives may be provided, as appropriate, for those participants who die, who discontinue intervention due to an AE, or who experience a severe or a serious AE.

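### Major malformations are counted only in infants from birth, so the comparison between groups is conditioned on reaching birth and misses anomalies in lost or terminated pregnancies

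*Protocol article*

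**What the plan says.** Table 1 of the protocol article (Outcomes {12}) has two primary endpoints. The neonatal/infant objective concerns "adverse neonatal/infant outcomes in neonates/infants" born to randomized women, and its endpoint covers "major congenital malformations, small for gestational age (SGA), low birth weight, preterm birth, neonatal death, and failure to thrive in infants measured from birth", with follow-up to 14 weeks of age. This is the only place where malformations are an endpoint.

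The maternal/fetal endpoint begins "Frequency of maternal death, spontaneous abortion, stillbirth, pathways to preterm birth" and continues through "provider initiated preterm birth), pre-eclampsia/eclampsia, antenatal bleeding and post-partum hemorrhage from randomization until 6 weeks post-completion/termination of pregnancy". It names neither fetal malformation nor induced termination. The word termination serves there only to mark the end of the observation window.

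Statistical methods {20a} summarizes women for whom "at least one of the indicated adverse outcomes was reported as a primary endpoint", and then each outcome separately. An outcome on neither list is therefore not a primary event.

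The secondary rows of Table 1 add all SAEs in women, all SAEs in newborns (again starting at birth) and a description of pregnancy outcomes, illustrated by "Pregnancy outcomes (example: normal delivery, Caesarian Section". The birth-outcome categories in Table 5, footnote d, are "Live birth, stillbirth, neonatal death, parity", with no entry for induced termination or spontaneous abortion.

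**The concern.** The benefit-risk section of the article describes the theoretical risk to mother and infant as unknown, and the Objectives section says the result is meant to support relaxing the restriction on use in pregnancy. A malformation count that starts at birth selects on an outcome that exposure could change. If vaccination caused malformations that often ended the pregnancy, the infants left to be counted would understate the effect.

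The endpoint is also narrower than the evidence it extends. The sponsor's review of 79 exposed pregnancies (section on vaccination during pregnancy) reported on malformations in fetuses as well as newborns.

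The trial is open-label, so decisions to end a pregnancy could differ between groups. That would make the loss from the malformation count differential.

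**Working it through.** **1. Where an affected pregnancy is counted, from Table 1 and Table 5 as printed.** Enrolment is limited to singleton pregnancies, so a pregnancy and a fetus are the same unit.

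| How the pregnancy ends | Primary maternal/fetal event? | Counted as a malformation? |
|---|---|---|
| Live birth | Only if a listed event also occurs | Yes |
| Stillbirth | Yes | Not clear |
| Spontaneous abortion | Yes | No |
| Induced termination, no other listed event | No, unless a late induction is classed as provider-initiated preterm birth, which the article does not settle | No |

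**2. The plan's own figures (Sample size {14}).** With 1000 women and a true rate of 1/1000, P(at least one event) = 1 − (1 − 0.001)^1000 = 63.2%, against 63% stated. With no event seen, the one-sided exact 95% upper bound is 1 − 0.05^(1/1000) = 0.299%, against 0.3% stated. Both reproduce. Both apply only to events that are counted.

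**3. If a share f of affected pregnancies never reaches the malformation count.** The document does not give f; the values below are assumptions. The chance of counting at least one case in 1000 at a true rate of 1/1000 is 1 − (1 − 0.001 × (1 − f))^1000. The bound on the true rate with none counted is 0.299% / (1 − f).

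| f (assumed) | P(at least one counted) | Upper bound if none counted |
|---|---|---|
| 0 | 63.2% | 0.30% |
| 10% | 59.4% | 0.33% |
| 25% | 52.8% | 0.40% |
| 50% | 39.4% | 0.60% |
| 75% | 22.1% | 1.20% |

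Here f describes the malformation row only. Any of these cases that ends as an abortion or stillbirth is still a primary event under its own heading.

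**4. Effect on the comparison.** Suppose malformations truly doubled in group A (a ratio of 2.0). The counted ratio is 2 × (1 − f_A) / (1 − f_B).

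- Equal shares, 10% and 10%: 2 × 0.90 / 0.90 = 2.0, no distortion.
- 25% in A, 10% in B: 2 × 0.75 / 0.90 = 1.67.
- 50% in A, 10% in B: 2 × 0.50 / 0.90 = 1.11.

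An equal loss in both groups costs cases but leaves the ratio alone. The ratio is distorted only if the loss differs by group.

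**5. How often this could arise.** The Discussion expects 1.5% to 4.25% of women to enrol in the first trimester. That is 0.015 × 1000 = 15 to 0.0425 × 1000 = 42.5, or about 15 to 43 women in group A if the share is equal in both groups. The article puts the end of the first trimester at week 13. Ultrasound is scheduled in both groups at nominal day 85, which is 84 days, or 12 weeks, after randomization. For the remaining 95.75% to 98.5% of women the scan falls at about week 25 or later, or week 24 at the early edge of the ± 7-day window. Eligibility also requires evidence of normal gestation before randomization, including fetal ultrasound. The article gives no rate of malformation or of termination for anomaly, so no expected number of cases can be derived.

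**The case against.** The strongest reply is that little harm would be hidden. Spontaneous abortion and stillbirth are primary outcomes in both groups, so a vaccine effect lethal in utero would show as an excess of primary events, only without its cause. A reader might infer from the endpoint wording that the most severe fetal harm could pass through the trial with no primary event at all. The documents do not support that in general. It fits only an induced termination with no other listed event, and a late one might still be classed as provider-initiated preterm birth.

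A reader might also infer that malformed stillborns are definitely excluded. That goes too far. The endpoint does not say live-born, and Table 5 schedules the neonatal examination and the adverse neonatal/infant outcomes at the pregnancy completion/termination visit, where stillbirth is a recorded category. The text is unclear on stillbirths; it does not exclude them.

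Three further points carry weight. The article relies on Brighton Collaboration case definitions and on a fuller protocol, neither shown, and these may settle the matter. Terminations can be recorded as maternal SAEs or under the description of all pregnancy outcomes. Because no hypothesis is tested, moving an item between primary and secondary changes emphasis, not error rates.

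These points limit the size of the concern. They do not remove it. The secondary routes give no malformation count, and the only examples for pregnancy outcomes are modes of delivery. If the definitions not shown are broader, the printed endpoint still confines the count to infants from birth, and the two should be brought into line.

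The reply also limits the remedy. Induced termination can be a matter of choice, and women know their group, so it need not become a primary adverse outcome. No schedule lists examination of fetal tissue after an early loss, and none should be assumed.

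**Conclusion.** The point holds in limited form. As printed, the malformation comparison is conditioned on reaching birth. A malformed fetus lost as a spontaneous abortion is a primary event without a malformation count, the status of a malformed stillborn is unclear, and an induced termination for anomaly with no other listed event reaches only secondary data.

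The size cannot be computed from the document. It is probably small, given 1.5% to 4.25% first-trimester enrolment and a post-randomization scan at about week 24 to 25 or later for more than 95% of women. The detection probabilities of 53% to 39% and the counted ratios of 1.67 and 1.11 are illustrations resting on assumed loss shares, and the ratios also assume that these shares differ by group. The conclusion rests on the wording of Table 1, Table 5 and Statistical methods {20a}, and would shrink to a wording correction if the full protocol already counts malformations over all pregnancy outcomes. This is a cheap improvement, not a fault that undermines the trial.

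**What to change.** Define the malformation endpoint over all pregnancies with known outcome: live birth, stillbirth, spontaneous loss and induced termination. Use findings already available from the scheduled obstetric ultrasounds and from the examination at pregnancy completion/termination. Report live-born cases as a sub-row, so that the count as now printed remains visible.

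Tabulate induced terminations with their reason, by group, next to the primary fetal outcomes, without making them a primary adverse outcome. State how the case definitions in use treat stillbirths and terminations.

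The cost is endpoint wording, one table, and whatever CRF entry is needed for fetal anomaly and reason for termination; the CRF is not shown, so that last part cannot be verified. No new fetal examination is required. The downside is less certain ascertainment in early losses, which the live-born sub-row makes visible.
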